### Confidentiality {27}

All records containing personal information will be stored separately in the database and will only be shared within the study for research purpose. Only healthcare professionals and investigators have access to the information necessary for conducting the intervention. Data analyst will be blinded to the allocation of groups.

### Plans for collection, laboratory evaluation, and storage of biological specimens for genetic or molecular analysis in this trial/future use {33}

There is no plan for biological specimen collection and analysis in this trial.

## Statistical methods

### Statistical methods for primary and secondary outcomes {20a}

Statistical analysis will be conducted using R (version 4.2.0; R Foundation for Statistical Computing). We will use a two-sided significance level of 5% and report the results with two-sided 95% confidence intervals (CIs) for all statistical analyses. For continuous variables, the Shapiro-Wilk test and Levene’s test will be utilized to identify the appropriate data treatment (i.e., parametric or non-parametric analysis), followed by a descriptive analysis presenting as means (SD) or median (IQR). Categorical variables will be presented as frequencies (percentages). For the statistical analysis of repeated outcome measures, generalized linear mixed models (GLMMs) will be used. These models are well-suited for our study design as they can effectively handle the complexities of repeated measures data and accommodate various response variable distributions, including normal, nonnormal, and ordinal categorical responses [37–39]. The primary fixed effects in our models will be the intervention and the time. To account for individual variability among participants, random effects will be included in the model to capture the individual variation. We will adjust for potential confounders that might influence the relationship between the intervention and the outcomes. These confounders include both basic demographics (age, gender, and education level) and heatlh-related factors (physical activity level, diet, smoking status, and medication use). We will further consider the inclusion of interaction terms in our model to examine if the effect of the intervention varies across different levels of confounders.

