### Trial design {8}

This experimental study expected to run from July 2023 to September 2024 will follow a non-blinded, paralleled, two-arm pre-test post-test design including 150 community-dwelling elders. This trial will be conducted simultaneously in six community health service centers within Nanhu district, Jiaxing City, located in Zhejiang province, China. Following a cluster randomization design, intervention and control sites will be allocated in a 1:1 ratio based on a randomized allocation sequence generated by a single investigator using R 4.2.0 The intervention period is expected to last for 6 months, following a preparation and recruitment phase. Effect measurements will be conducted at three time points: at the beginning, after 3 months, and after 6 months of the intervention. Implementation measurements will be carried out throughout the study. The trial design follows the SPIRIT checklist (Additional file 1).

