### Outcomes {12}

The primary outcome is the dietary behavior changes, specifically defined as dietary diversity, diet quality, and adherence to dietary interventions, from baseline (T0) to 3 months (T1) and 6 months (T2). The key secondary outcome is the perceived acceptability and usability of personalized meal recommendations as a dietary intervention specifically in the intervention group. The exploratory outcomes are nutritional status and anthropometric measurements of the community-dwelling elders.

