## Data collection and management

### Plans for assessment and collection of outcomes {18a}

All primary and secondary outcomes will be repeatedly measured at baseline, 3 months, and 6 months. System usability and satisfaction will only be evaluated in the intervention group, while dietary behaviors (dietary diversity and diet quality, adherence to the interventions), nutritional status, and anthropometric measurements will be evaluated in both the intervention and control groups. Detailed information on data collection methods is shown in Table 2.

**Table 2 Tab2:** The outcome measures and collecting methods

**Outcome measure**		**Collection method**
Dietary behavior	Dietary diversity	IoT system log, DDS
	Diet quality	IoT system log, CDGI-E
	Recommendation adherence	IoT system log
System usability and satisfaction	Satisfaction ratings	Questionnaire (CSAT)
	Ease of use ratings	Questionnaire (CES)
Nutritional status	Risk of malnutrition	Questionnaire (MNA-SF)
Anthropometric measurements	Body mass index	Basic body measurement (body weight scale, height rod)
	Waist circumference	Basic body measurement (measuring tape)
	Systolic blood pressure	Blood pressure monitor
	Diastolic blood pressure	Blood pressure monitor
	Skin folds	Basic body measurement (skinfold caliper)

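### As written, the primary mixed model's intervention effect averages in the T0 visit, so for DDS and CDGI-E it does not estimate the stated change from T0

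*Protocol article*

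**What the plan says.** All references are to the protocol article.

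- **Outcomes {12}** defines the primary outcome as change in dietary behavior "from baseline (T0) to 3 months (T1) and 6 months (T2". Its components are dietary diversity, diet quality and adherence.
- **Plans for assessment and collection of outcomes {18a}**: "All primary and secondary outcomes will be repeatedly measured at baseline, 3 months, and 6 months".
- **Trial design {8}**: "Effect measurements will be conducted at three time points: at the beginning, after 3 months, and after 6 months of the intervention". **Sample size {14}** likewise counts three repeated measurements (k = 3).
- **Statistical methods for primary and secondary outcomes {20a}** gives the model: "For the statistical analysis of repeated outcome measures, generalized linear mixed models (GLMMs) will be used". On its terms it says "The primary fixed effects in our models will be the intervention and the time", and "random effects will be included in the model to capture the individual variation". It lists confounders to adjust for, among them an undefined entry for diet, and says the authors will consider "interaction terms in our model to examine if the effect of the intervention varies across different levels of confounders".

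Section {20a} names no intervention-by-time term and no contrast against T0. It does not name the participant's own T0 score as a covariate.

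**The concern.** A between-arm difference in change from T0 is an intervention-by-time contrast. Suppose T0 is one of the responses and the model has main effects of intervention and time. The intervention coefficient is then a single arm difference assumed constant over all visits, and it is estimated by averaging the three visit differences. At T0 the intervention has not yet acted, so a visit with no possible effect enters the average.

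Three things follow. The reported coefficient is not the stated outcome. It is pulled towards zero when the intervention works. And a pre-existing difference between the arms is counted as effect, so it can also produce a false positive. That last risk is real here: only six sites are randomized 1:1, and participants are recruited by convenience sampling.

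**Working it through.** **Inputs**, from Sample size {14}: δ = 2.3, σ = 6.12 (σ² = 37.454), ρ = 0.7, k = 3, two-sided α = 5%, n = 60 per arm.

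**The plan's own figure.** The printed formula gives 2 × (1.960 + 0.842)² × 37.454 / (3 × 2.3²) = 37.05, so 38 per arm and not 60. The attrition step does reproduce: 120/0.8 = 150. The gap between 38 and 60 is a separate matter. I take 60 per arm as stated; the size of the dilution does not depend on it.

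**What the main-effects model targets.** With a random participant intercept, categorical time and complete data, the arm coefficient equals the arm difference in participant means over the three visits:

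- expected value = (d0 + d1 + d2)/3, where d0, d1 and d2 are the true arm differences at T0, T1 and T2
- benchmark d = (0, 2.3, 2.3): 4.6/3 = 1.533, which is 0.667 of 2.3
- this does not depend on ρ (0.3 to 0.9 all give 1.533)

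**Standard errors and power.** Each estimate has SE = √(2σ²f/n) = √(1.2485 f). The factor f depends on the analysis. Power = Φ(estimate/SE − 1.96).

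| Analysis | f | Target | SE | Power |
|---|---|---|---|---|
| Main effects, T0 as a response | (1 + 2ρ)/3 = 0.80 | 1.533 | 0.999 | 34% |
| Mean of T1 and T2 minus T0 | (1 + ρ)/2 + 1 − 2ρ = 0.45 | 2.3 | 0.750 | 87% |
| Mean of T1 and T2, adjusted for T0 | (1 + ρ)/2 − ρ² = 0.36 | 2.3 | 0.670 | 93% |
| T2 alone, adjusted for T0 | 1 − ρ² = 0.51 | 2.3 | 0.798 | 82% |
| T2 minus T0 | 2(1 − ρ) = 0.60 | 2.3 | 0.865 | 76% |

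A check with 800 simulated trials, each fitted with the main-effects mixed model, gave a mean coefficient of 1.533 (Monte Carlo SE 0.035) and power of 34%.

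**Away from the benchmark.**

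- Effect that builds up (0, 1.15, 2.3): coefficient 1.15, half the T2 effect.
- Effect at T2 only (0, 0, 2.3): coefficient 0.77, one third of the T2 effect.
- 75 per arm with 20% dropout (assumed half after T0 and half after T1), equal effects of 2.3: the coefficient is 0.59 to 0.60 of the effect for ρ from 0.5 to 0.9.

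**Baseline imbalance.** A difference D present at all three visits with no treatment effect gives (D + D + D)/3 = D; D = 1 gives an estimate of 1.0. The change contrast gives (D + D)/2 − D = 0.

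**The case against.** The strongest reply is that section {20a} does not print a model equation. Calling two fixed effects primary may only name the variables of interest, and the same paragraph goes on to covariates and possible interactions. The article condenses a fuller plan, in which the tested contrast may be written out. Three readings would soften or remove the problem:

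- **Changes from T0 are the response.** Arm and time as fixed effects would then target 2.3, with SE 0.750 and power of about 87%.
- **Intervention is coded zero at T0.** The pre-treatment visit would then not dilute the coefficient.
- **The diet confounder means the T0 diet score.** Baseline dietary behaviors are collected (Implementation {16c}), so this is possible. It would address imbalance. It would not address dilution while T0 stays among the responses, because the average would still contain a visit with no effect.

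Part of this stands. The article does not rule out an intervention-by-time term, and a reader who infers that the authors have committed to excluding one goes further than the text. But none of the three readings is stated. Section {20a} applies the model to the repeated measures, which other sections define to include T0. It also takes up interactions and gives them a different purpose. So the text is more than silent: followed literally, it yields the wrong contrast.

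A reader might also infer that all three primary components are affected. The argument reaches DDS and CDGI-E only, since adherence to recommended meals has no natural pre-treatment value.

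**Conclusion.** The point holds for DDS and CDGI-E. Read as written, the named intervention effect does not estimate the primary outcome of Outcomes {12}, and it carries in any T0 imbalance.

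In the benchmark case it targets 1.53 instead of 2.3. That rests on equal effects at T1 and T2, complete data and a constant arm indicator. A reader might take one third as the dilution in all circumstances, but it depends on those assumptions: relative to the T2 effect the loss is larger when the effect builds up over time, and with dropout it is also larger.

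The power figures ignore clustering across six sites, so they rank the analyses and do not give this trial's actual power. A reader might also set 34% against 93% as the gain from any repair. The 93% belongs only to the T1/T2 average adjusted for T0; the change contrast over T1 and T2 gives 87%, and T2 alone adjusted for T0 gives 82%. Nor do the documents make T2 the primary time point: Outcomes {12} names T1 and T2 without ranking them.

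**What to change.** In {20a}, for DDS and CDGI-E, state one of the following:

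1. T0, T1 and T2 are the responses; the fixed effects include intervention, time and intervention-by-time; the primary test is the between-arm contrast in change from T0 to T1 and from T0 to T2, or their average.
2. T1 and T2 are the responses, with the participant's T0 score as a covariate, or equivalently a longitudinal model with a common T0 mean in both arms; the primary test is the adjusted arm difference at T1, at T2 or averaged over both.

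Whether T1, T2 or their average is primary is the sponsor's choice, but it should be written down before analysis. Adherence needs its own statement, since it has no T0 value to contrast with.

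The cost is analysis wording only. No new data are needed, because the T0 scores are already collected.

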### Sample size {14}

This study uses a randomized, non-blinded, two-armed study design with three times measurements during the study. The power calculation is based on the primary outcome measure- dietary diversity score. The sample size was calculated according to the repeated-measures formula [24, 25]: *N* = $$\frac{2{({{\text{Z}}}_{1-\mathrm{\alpha }/2}+ {{\text{Z}}}_{1-\upbeta })}^{2} {\upsigma }^{2}}{k{\updelta }^{2}}$$. In this formula, parameters denoting the number of repeated times *k* = 3, type I error rate *α* = 5% (two-sided), and a power level of 0.80. We set the smallest detected meaningful difference *δ* = 2.3 according to experts’ experience. Based on the results of relevant studies and our baseline survey, the correlation coefficient among measures *ρ* = 0.7, and equal standard deviation *σ* = 6.12 was used [24, 26]. It was estimated that the desired number of included participants at baseline should be set at a minimum of 60 for each arm. Consequently, a total of 150 community-dwelling elderly individuals are expected to recruit at baseline considering an attrition rate of 20% [27–29].

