## Assignment of interventions: allocation

### Sequence generation {16a}

Under the cluster randomization design, one investigator will generate a randomized allocation sequence using R 4.2.0 to allocate the intervention and control sites at a 1:1 ratio. The investigator tasked with generating the randomization sequence is specifically chosen for non-involvement in the recruitment of centers or the collection of participant data.

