### Implementation {16c}

An investigator will use a randomization algorithm to allocate six candidate sites to different groups, ensuring random and unbiased assignment. The results will be informed to the social workers at respective sites. At each site, social workers will be responsible for recruitment and conducting baseline assessments. All subjects who have provided informed consent will be included in the trial. The social workers will guide the enrollment session, explaining the intervention assignment process to the participants. Following enrollment, the overarching purpose of the study, intervention procedures in the assigned group, and measurement details will be thoroughly explained to each participant. Additionally, each participant will undergo a baseline assessment that includes collecting information on socio-demographics, dietary behaviors, anthropometric characteristics, medical history, and nutritional status.

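### Six sites are randomised, but the primary mixed model has random effects for participants only, so the 5% error rate and 95% intervals fail unless sites do not differ

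*Protocol article*

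**What the plan says.** The unit of randomisation is the site. Trial design {8} states: "Following a cluster randomization design, intervention and control sites will be allocated in a 1:1 ratio". Sequence generation {16a} repeats it: "Under the cluster randomization design, one investigator will generate a randomized allocation sequence using R 4.2.0 to allocate the intervention and control sites". Implementation {16c} gives the number: "An investigator will use a randomization algorithm to allocate six candidate sites to different groups". At 1:1 that is three sites against three.

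The analysis is set out in the statistical methods section {20a}. Repeated outcomes go into generalized linear mixed models, and the reason given for that choice is repeated measurement and varied outcome distributions. On fixed effects: "The primary fixed effects in our models will be the intervention and the time". On random effects: "To account for individual variability among participants, random effects will be included in the model to capture the individual variation". On error control: "We will use a two-sided significance level of 5% and report the results with two-sided 95% confidence intervals (CIs) for all statistical analyses".

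The sections on additional analyses {20b} and on non-adherence and missing data {20c} add subgroup models, intention-to-treat and per-protocol analyses, and multiple imputation. Neither mentions site.

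**The concern.** Everyone at a site is in the same arm. Whatever makes one site's participants eat differently from another's therefore feeds into the arm comparison. Such differences are likely here. Dietary diversity and diet quality are computed from logged canteen dish choices, the sites lie in different areas, participants are a convenience sample from each community, and site social workers recruit and assess at baseline. Adjusting for age, education and similar personal factors cannot be relied on to remove this.

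A participant random effect handles the correlation among one person's three visits. It does nothing for the correlation among people at one site. The model then makes two errors: its standard error is too small, and it refers the result to a normal or large-df distribution when only 6 − 2 = 4 degrees of freedom exist between sites within arms. A significant result could be a site difference reported as an intervention effect.

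**Working it through.** **Inputs from the protocol article.** Six sites, 3 v 3 ({8}, {16c}). 150 recruited with 20% attrition ({14}), so 150/6 = 25 per site at baseline and 25 × 0.8 = 20 at the end, taking sites as equal. Three measurements, within-person correlation 0.7, SD 6.12 and target difference 2.3 ({14}). Two-sided 5% ({14}, {20a}).

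**Assumed.** Site ICC 0.01 to 0.10, because the article gives none.

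**The plan's own figure.** The claim to test is the 5% level. Simulated data with no site variance, fitted with a participant intercept only (25 per site, 300 trials), gave 4.3% rejections. That is compatible with 5%, so the model works when sites do not differ.

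**Single-measure approximation.** The true variance exceeds the model's by the design effect DE = 1 + (m − 1) × ICC, and the actual error rate is 2 × [1 − Φ(1.96/√DE)].

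**Three-visit main effect.** With only intervention and time as stated primary fixed effects, the tested quantity is the arm difference averaged over visits. With total variance 1, a participant's three-visit mean has variance 0.7 + 0.3/3 = 0.8, so the ICC of the means is ICC/0.8 and DE = 1 + (m − 1) × ICC/0.8.

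| m per site | ICC | Single-measure DE | Error | Three-visit DE | Error by formula | Error by simulation (40,000 trials) |
|---|---|---|---|---|---|---|
| 20 | 0.01 | 1.19 | 7.2% | 1.24 | 7.8% | 7.7% |
| 20 | 0.05 | 1.95 | 16.0% | 2.19 | 18.5% | 18.4% |
| 20 | 0.10 | 2.90 | 25.0% | 3.38 | 28.6% | 29.1% |
| 25 | 0.01 | 1.24 | 7.8% | 1.30 | 8.6% | 8.5% |
| 25 | 0.05 | 2.20 | 18.6% | 2.50 | 21.5% | 21.5% |
| 25 | 0.10 | 3.40 | 28.8% | 4.00 | 32.7% | 33.3% |

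Mixed models actually fitted at ICC 0.05 with 25 per site (300 trials) rejected 21.0%. A t-test on the six site means (4 df) rejected about 5.0% at every ICC.

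**Change from baseline.** A constant site effect cancels from a change score, but site-specific drift does not. Let s be the site-by-time share of variance. A change between two visits has total variance 2 × (1 − 0.7) = 0.6, of which 2s lies between sites, so its ICC is 2s/0.6.
- s = 0.005: ICC 0.0167, DE 1.32 (m = 20) to 1.40 (m = 25), error 8.8% to 9.8%.
- s = 0.02: ICC 0.0667, DE 2.27 to 2.60, error 19.3% to 22.4%.

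**Interval width.** At 25 per site, the three-visit DE of 1.30 to 2.50 (ICC 0.01 to 0.05) means standard errors should be √1.30 = 1.14 to √2.50 = 1.58 times larger. The critical value on 4 df is 2.78, not 1.96. Together these give 1.14 × 2.78/1.96 = 1.6 to 1.58 × 2.78/1.96 = 2.2 times the width.

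**Power of an analysis that respects sites.** With 25 per site, SE = 6.12 × √[(2/3) × (ICC + (0.8 − ICC)/25)], which is 1.02 at ICC 0.01 and 1.41 at 0.05. For a difference of 2.3 and a t-test on 4 df, power is 41% and 24%.

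**Exact randomisation test.** C(6,3) = 20 allocations, so the smallest two-sided p-value is 2/20 = 0.10. This route cannot reach 5%.

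**The case against.** **The outcome is a change.** Outcomes {12} defines the primary outcome as change from baseline to 3 and 6 months, and persistent site differences cancel from a change. That is correct, and the main-effect error rates do not carry over to such a contrast. But {20a} names only intervention and time as primary fixed effects, and the interaction terms it mentions concern confounders. The main-effect reading therefore follows from the text. On the change reading, modest site-by-time variance produces similar inflation.

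**No ICC is given.** This stands. The percentages are scenarios, and at zero site variance the 5% level holds.

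**A separate analysis plan may add a site term.** It may, but the article is not silent. It states what the random effects are for and justifies the model by repeated measurement alone, in conflict with its own design.

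**Six sites barely identify a site variance.** This also stands. In a balanced layout the estimate is zero in roughly 47-49% of trials at ICC 0.01 and 22-26% at 0.05. It is not a reason to omit the term: with small-sample degrees of freedom, the rejection rate stays close to 5% or below even with such zero estimates. It does favour a site-level analysis as the simpler choice.

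**The mixed model and the site-mean t-test are different analyses, and Kenward-Roger or Satterthwaite corrections belong to linear mixed models.** Both points are right. The fix has to treat them as alternatives and provide separately for ordinal and other non-normal outcomes.

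**Conclusion.** The concern holds. The stated model contradicts the stated randomisation, and its p-values and intervals are valid only if sites do not differ. For the intervention main effect, with equal sites of 20 to 25, three visits and within-person correlation 0.7, the actual two-sided error is about 8-9%, 18-22% and 29-33% at site ICC 0.01, 0.05 and 0.10. The single-measure formula gives the somewhat lower 7-8%, 16-19% and 25-29%. For a change contrast, site-by-time variance of 0.5% to 2% of the total gives about 9% to 22%. All of these rest on assumed variance shares. The direction does not: any positive site-level variance in the tested contrast pushes the error above 5%. Because this is the primary analysis, it must be corrected before the data are analysed.

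**What to change.** Amend {20a} to state the following:

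- Sites are the randomised units, and the model includes a random intercept for site, a site-by-time random effect and the participant effect nested in site. The site-by-time term is needed because a site intercept alone drops out of change contrasts.
- For normal outcomes, inference uses Kenward-Roger or Satterthwaite degrees of freedom. The site terms stay in the model even if a variance is estimated as zero.
- Alternatively, and as the option for non-normal or ordinal outcomes, site-level summaries are compared by a t-test on 4 df. If baseline is adjusted for by regressing on site means, 3 df remain. Choose one approach as primary in advance.
- Site is not entered as a fixed effect, because it is confounded with arm. Wald z-tests and uncorrected robust errors are not used with six clusters.
- The imputation model in {20c} includes site, and the subgroup models in {20b} use the same structure.

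This costs a few sentences and no new data. The real price is precision: intervals about 1.6 to 2.2 times as wide and power of about 24% to 41% for a difference of 2.3 (ICC 0.05 to 0.01, 25 per site), against the 80% planned. That shortfall comes from having six sites. The participant-only model hides it, and the trial report should acknowledge it.
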